#### **13.4.4 Drug Accountability**

The investigational sites will be provided with sufficient amounts of investigational medicinal products. The investigational medicinal products must not be used outside the study protocol. The investigator or authorized staff is obliged to acknowledge receipt of the study medication to confirm the content and shipping temperature. Any damaged shipment of study medications will be replaced. The study drug will be disposed of in accordance with the standard operating procedures at the study site, or returned to the sponsor with appropriate documents. The investigational site's method of study medication destruction must be agreed to by the Sponsor.

Before destroying any study medications, the investigational site must obtain the written authorization from the sponsor and document the destruction of study medications in an appropriate form. Accurate records of receipt, dispensation, return and disposition of all study medication during the study should be documented on the drug inventory log.

#### **14. Study Schedule**

The schedule of assessments conducted during the study is shown in Part 2 of Chapter

2. Flow Chart and Schedule of Assessments. The study includes three periods:

Screening (V0), treatment (V1, V2) and Follow up (V3, V4).

#### **14.1 Screening period (Visit V0, Randomization)**

##### **14.1.1 Visit V0**

For each eligible patient, written informed consent for participation in the study will be obtained from the patient or the patient's legal representative prior to the performance of any protocol-related investigation. Once written informed consent is obtained, the results of the following standard of care assessments will be used for the study. The investigator will record the details of all patients consented to confirm eligibility and record the reasons for screening failure.

- Demographics
- Medical history
- Physical examination
- Determination of the pre-stroke mRS via interview of the patient or the patient's kin
- NIHSS score (Note: performed by an NIHSS-certified practitioner)
- Collection of information on previous medications
- Measurement of blood pressure and heart rate
- Pregnancy test (urine test, in non-menopausal women)

- Laboratory tests
- A 12-lead ECG
- Non-contrast CT scan or MRI scan and CTA, MRA, or DSA
- Concomitant medications
- Checking of inclusion and exclusion criteria

#### **14.1.2 Randomization (R)**

If all inclusion criteria are met and no exclusion criteria are present, randomization will be performed.

#### **14.2 Treatment period (Visits V1, V2)**

- After randomization, the treatment period starts, including study medication (V1) and post-treatment clinical examination (V2).

##### **14.2.1 Visit 1**

Before administration of the study medication, measurement of blood pressure and heart rate have to be performed. The study medication will be administered as specified for intravenous methylprednisolone. During the administration of study medication, the following assessments will be made:

- Measurement of blood pressure and heart rate every hour.
- Documentation of any concomitant medication.
- Assessment of Adverse Event.

- In any case of significant neurological deterioration judged by the investigator, an assessment of the neurological deficit and another non-contrast cranial CT scan or MRI scan have to be performed to determine whether intracranial haemorrhage occurs.
- The 48h monitoring should be performed in Stroke Unit or equivalent unit.

#### **14.2.2 Visit 2**

- Visit 2 comprises the clinical examination and a second non-contrast cranial CT or MRI scan which is performed to diagnose intracranial haemorrhage. Visit 2 will be done 48-96h after the administration of study medication. The following assessments will be performed:

- Physical examination
- Assessment of the neurological deficit by the NIHSS
- Measurement of blood pressure and heart rate
- Laboratory tests
- Non-contrast cranial CT or MRI scan
- Documentation of any concomitant medication
- Assessment of Adverse Event

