**2.2. Schedule of Assessments**

|                                  | Visit (Time in hours / days from EVT =V1) |   |                                                       |                    |                               |               |
|----------------------------------|-------------------------------------------|---|-------------------------------------------------------|--------------------|-------------------------------|---------------|
|                                  | Screening                                 |   | Treatment                                             |                    | Follow Up                     |               |
|                                  | V0                                        | R | V1 a
Study medication
administration | V2
(48-
96h) | V3 b
(5-
7d) | V4
(90±7d) |
| Informed consent                 | X                                         |   |                                                       |                    |                               |               |
| Demographic data                 | X                                         |   |                                                       |                    |                               |               |
| Medical history                  | X                                         |   |                                                       |                    |                               |               |
| Physical examination             | X                                         |   |                                                       | X                  | X                             |               |
| Pre-stroke mRS                   | X                                         |   |                                                       |                    |                               |               |
| NIHSS                            | X                                         |   |                                                       |                    | X                             |               |
| mRS                              |                                           |   |                                                       |                    |                               | X             |

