| EQ-5D                            |                                           |   |                                                       |                    |                               | X             |
| Previous medication              | X                                         |   |                                                       |                    |                               |               |
| Blood pressure and heart
rate | X                                         |   | X                                                     | X e     | X                             |               |
| Local laboratory result          | X                                         |   |                                                       | X                  |                               |               |
| Pregnancy test c      | X                                         |   |                                                       |                    |                               |               |

|                                   |   |   |                |   |   |   |
|-----------------------------------|---|---|----------------|---|---|---|
| Brain CT/MRI plus
CTA/MRA/DSA  | X |   |                |   |   |   |
| Brain CT/MRI scan d    |   |   |                | X |   |   |
| Inclusion / exclusion
criteria | X |   |                |   |   |   |
| Randomization                     |   | X |                |   |   |   |
| Study medication                  |   |   | X              |   |   |   |
| Concomitant medication            | X |   | X              | X | X | X |
| 12-lead ECG                       | X |   |                |   |   |   |
| 48h monitoring                    |   |   | X a |   |   |   |
| Adverse events                    |   |   | X              | X | X | X |

V = Visit; R = Randomization; h = hour; d = day

a 48h monitoring in Unit or equivalent unit including repeated measurements of blood pressure, heart rate and body temperature

b or hospital discharge if < 5 days

c Mandatory for women of childbearing potential

d also to be performed in any case of neurological deterioration during the first 96h

e every hour

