## **15.3 Safety Analysis-Primary Endpoint**

### **15.3.1 Primary Safety Endpoints**

- Mortality due to any cause at 90 (±7) days;
- Proportion of patients with symptomatic intracranial haemorrhage within 48 hours after endovascular treatment. Symptomatic intracranial haemorrhage will be adjudicated by an independent Imaging Core Laboratory and the Clinical Events Committee according to the modified Heidelberg Bleeding Classification, and is diagnosed based on a combination of: 1) clinical deterioration, 2) imaging findings, and 3) causal relatedness assessment. Clinical deterioration is defined as any of the following conditions: 1) NIHSS score increased more than 4 points than that

immediately before worsening; 2) NIHSS score increased more than 2 points in one category; 3) Deterioration led to intubation, hemicraniectomy, external ventricular drain placement or any other major interventions. The imaging criteria are presence of parenchymal hematoma type 2 (PH2), parenchymal hematoma type 1 (PH1), remote intracerebral haemorrhage (RIH), subarachnoid haemorrhage (SAH), intraventricular haemorrhage (IVH), or subdural haemorrhage. When clinical deterioration and PH2 co-occur, the event is automatically categorized as SICH. When clinical deterioration and PH1/RIH/SAH/IVH/SDH co-occur, the event is deemed SICH if it is judged that the haemorrhage contributed substantially to the clinical worsening. When clinical deterioration occurs only with haemorrhagic infarction type 1 or 2 (HI1 or HI2), the event is automatically classified as not SICH. ICH.

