### **15.3.2 Secondary Safety Endpoints**

- Proportion of patients with any radiologic intracranial haemorrhage within 48 hours after treatment;
- Proportion of patients with pneumonia;
- Proportion of patients with gastrointestinal haemorrhage within 7 days after EVT;
- Incidence of serious adverse events.
- Incidence of any adverse events.

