### **18.4 Safety analysis**

Safety outcomes include incidence of overall mortality at 90 ( $\pm$ 7) days after randomization, the proportion of patient with SICH within 48 hours after treatment, the proportion of patient with any ICH within 48 hours after treatment, proportion of patients with pneumonia and proportion of patients with gastrointestinal haemorrhage within 7 days after EVT;. The safety analysis will be performed on the Safety

Population. The incidences of each outcome will be compared via Chi-square test or Fisher's exact test. The modified Poisson regression models will be fitted to estimate the risk-ratio associated with the treatment effect. Risk ratio with 95% CI will be reported. Patients with missing outcome will not be included in the regression analysis. Additionally, Log-Rank test and the Kaplan-Meier estimates will be plotted over the observation period of 90 days for mortality. Cox regression model will be employed to calculate the hazard ratio with 95%CI.

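### The 48-hour window for any radiologic haemorrhage closes as the window of the only scheduled follow-up scan (48–96 h) opens

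*Supplement*

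**What the plan says.** All references are to protocol version 2.0; no statistical analysis plan (SAP) is included in the material.

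- **Scheduled scan.** Section 14.2.2 describes "a second non-contrast cranial CT or MRI scan which is performed to diagnose intracranial haemorrhage" and sets the timing: "Visit 2 will be done 48-96h after the administration of study medication". In the schedule of assessments (section 2.2), the row "Brain CT/MRI scan" is marked at Visit 2 only.
- **Clock in the schedule.** The table heads its columns "Visit (Time in hours / days from EVT =V1", so there the 48–96 h run from EVT, not from study drug.
- **Unscheduled scans.** A footnote to the same row says that the scan is "also to be performed in any case of neurological deterioration during the first 96h". Section 14.2.1 likewise requires a scan for significant deterioration as judged by the investigator.
- **Secondary safety endpoint.** Section 15.3.2: "Proportion of patients with any radiologic intracranial haemorrhage within 48 hours after treatment". Sections 1, 16.2.3 and 18.4 repeat the 48 h limit. Section 16.2.3 includes haemorrhagic infarction types 1 and 2 among the subtypes and asks for no symptoms.
- **Primary safety endpoint.** Section 15.3.1: "Proportion of patients with symptomatic intracranial haemorrhage within 48 hours after endovascular treatment". Its definition requires clinical deterioration as well as imaging findings.

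**The concern.** The scan meant to diagnose haemorrhage is timed to begin when the any-haemorrhage endpoint stops counting. An endpoint that includes silent bleeds needs imaging of patients without symptoms inside its window, and the schedule provides essentially none.

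The protocol gives no rule for a bleed first seen at Visit 2, so the analyst must choose between two different endpoints:

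- **Literal reading.** Only bleeds imaged by 48 h count. The endpoint becomes mainly a record of findings in patients who deteriorated and were scanned for that reason, and most silent bleeds drop out. Being scanned early then depends on deterioration, which treatment itself might influence.
- **Loose reading.** Visit 2 findings count, and the reported 48 h rate is really a rate up to 96 h.

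As written, that choice could be made after the data have been seen. It also affects the subgroup of patients with any radiological haemorrhage in section 18.6.

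**Working it through.** The plan gives no expected rate or power for this endpoint, so there is no figure to reproduce. The check compares the two time windows.

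**Inputs**

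- Endpoint window: 0 to 48 h (section 15.3.2), counted here from the end of EVT.
- Visit 2 scan window: 48 to 96 h, from EVT (section 2.2) or from study medication (section 14.2.2).
- First dose: recommended before arterial access closure and at most 2 h after it (section 13.4.1). Closure is taken here as the end of EVT.
- Course: 3 days (section 13.4.1).

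**Step 1: EVT as the clock for both.** The windows 0–48 h and 48–96 h meet only at exactly 48 h. Overlap: 0 h.

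**Step 2: Visit 2 counted from the first dose.** Let s be the time of the first dose minus the end of EVT, in hours. On the EVT clock the scan window is 48 + s to 96 + s.

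Overlap = max(0, min(48, 96 + s) − (48 + s)), and share = overlap / 48.

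| s (h), assumed | Scan window on EVT clock (h) | Overlap (h) | Share of scan window |
|---|---|---|---|
| −2 | 46–94 | 2 | 4.2% |
| −1 | 47–95 | 1 | 2.1% |
| 0 | 48–96 | 0 | 0% |
| +2 (permitted limit) | 50–98 | 0, with a 2 h gap | 0% |

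Each hour by which the first dose precedes the end of EVT adds one hour of overlap.

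**Step 3: Visit 2 counted from the last dose.** Section 14.2.2 does not say which dose starts the clock. With doses assumed at 0, 24 and 48 h, the scan window is 48 + 48 = 96 h to 96 + 48 = 144 h. Overlap: 0 h.

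Across these cases at least 100% − 4.2% = 95.8% of the scan window lies after the endpoint has closed.

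**Step 4: what imaging each endpoint needs.**

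- Any radiologic haemorrhage needs no symptoms, and the only imaging required before Visit 2 follows deterioration. Take a patient who stays stable and has a bleed on a Visit 2 scan at 60 h, with no scan since baseline. The bleed arose somewhere between 0 and 60 h, and nothing collected says on which side of 48 h. The literal reading scores no event; the loose reading scores one.
- Symptomatic haemorrhage needs deterioration, and deterioration requires a scan throughout the first 96 h. A case within 48 h should therefore be imaged when it occurs, whatever the timing of Visit 2.

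**The case against.** **In the plan's defence.** The schedule lists required scans and does not forbid clinical ones. The core laboratory reviews all images (section 7.2.4), so some silent bleeds could be caught early. A Visit 2 scan at exactly 48 h, or a little earlier on the EVT clock when the first dose came before the end of EVT, also falls inside. Visit 2 timing is the same in both blinded arms, so counting Visit 2 bleeds mainly mislabels the rate rather than biasing the comparison. A SAP might hold a classification rule. These points stand and limit the seriousness, but optional scans are not systematic ascertainment, and a rule in the SAP could not create imaging before 48 h.

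**A reading that would remove the conflict.** If the word treatment in section 15.3.2 meant the end of the 3-day course, the window would run to about 48 + 48 = 96 h after the first dose (doses assumed at 0, 24 and 48 h) and would take in Visit 2. Section 18.4, however, uses the same expression for symptomatic haemorrhage, which section 15.3.1 ties to endovascular treatment. The wording needs settling in any case.

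**Stronger readings that the documents do not support.**

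- A reader might infer that the primary endpoint, symptomatic haemorrhage, cannot be ascertained either. It can: deterioration is part of its definition and itself requires a scan. What remains is a smaller dependence on the investigator's judgement of what is significant (section 14.2.1).
- A reader might infer that patients who die before Visit 2 are lost from the analysis, since section 18.4 says: "Patients with missing outcome will not be included in the regression analysis". That sentence does not class early deaths as missing, and patients who deteriorated neurologically before death should have been scanned.
- A reader might infer a calculable loss of power. The documents give no haemorrhage rate and power only the mRS outcome (section 18.1), so no such figure can be derived.
- A reader might object that bleeding late in the course goes unrecorded. Adverse events are collected from Visit 1 to Visit 4 and compared between groups, and ending a window at 48 h is a design choice.

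**Conclusion.** The point holds for the secondary any-haemorrhage endpoint, which does not match the only scan scheduled to measure it. The overlap is nil on the EVT clock and 2 of 48 h (4.2%) with a first dose 2 h before the end of EVT. That 2 h is an assumption, and an earlier dose would give more overlap. How many bleeds would be missed or misdated cannot be computed from the documents.

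The clocks also disagree: EVT in the schedule, an unspecified treatment in section 15.3.2, and study medication with no stated dose in section 14.2.2. The primary symptomatic-haemorrhage endpoint does not share the ascertainment gap. This should be fixed before unblinding, but it does not threaten the primary efficacy analysis.

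**What to change.** Redefine the secondary endpoint as any radiologic intracranial haemorrhage on any scan from EVT through the Visit 2 scan (up to 96 h). Make the change in sections 1, 15.3.2, 16.2.3 and 18.4.

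Use one clock origin throughout and reconcile the schedule in section 2.2 with sections 14.2.2 and 15.3.2. If study medication is kept as an anchor anywhere, say whether the first or the last dose is meant.

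Leave the primary symptomatic-haemorrhage endpoint at 48 h after EVT. Symptomatic haemorrhage through Visit 2 may be added as a supportive analysis.

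The cost is wording in the protocol and the matching SAP text, with no extra scans and no change to scan timing. The downside is small: the any-haemorrhage rate becomes less directly comparable with trials that report 48 h rates.

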#### **14.3 Follow Up period (Visits V3, V4)**

The Follow Up period comprises the period of the subacute stage (day 5-7 or hospital

discharge) in Visit 3, and the final follow up examination  $90 \pm 7$  days in Visit 4.

### **14.3.1 Visit 3**

The following assessments will be performed:

- Physical examination
- Assessment of the neurological deficit by the NIHSS
- Measurement of blood pressure and heart rate
- Documentation of any concomitant medication
- Assessment of Adverse Event

### **14.3.3 Visit 4**

The following assessments will be performed:

- Physical examination (If the patients return to local hospital)
- Assessment of the neurological deficit by the NIHSS
- Assessment of functional status by the mRS
- Assessment of functional health status and quality of life by the EQ-5D scale
- Documentation of any concomitant medication
- Assessment of Adverse Event

## **15. Endpoints of the Clinical Trial**

### **15.1 Efficacy Analysis-Primary Endpoint**

The primary outcome was the ordinal mRS score, a global measure of disability, comprises of seven grades ranging from 0 (no symptoms) to 6 (death).

## **15.2 Efficacy Analysis-Secondary Endpoints**

- Proportion of patients with mRS score 0 to 4 at 90±7 days;
- Proportion of patients with mRS score 0 to 3 at 90±7 days;
- Proportion of patients with mRS score 0 to 2 at 90±7 days
- Proportion of patients with mRS score 0 to 1(or returned to pre-stroke modified Rankin scale score) at 90±7 days
- NIHSS score at 5-7 days after EVT or at early discharge;
- European Quality Five-Dimension scale score at 90 days.

## **15.3 Safety Analysis-Primary Endpoint**

### **15.3.1 Primary Safety Endpoints**

- Mortality due to any cause at 90 (±7) days;
- Proportion of patients with symptomatic intracranial haemorrhage within 48 hours after endovascular treatment. Symptomatic intracranial haemorrhage will be adjudicated by an independent Imaging Core Laboratory and the Clinical Events Committee according to the modified Heidelberg Bleeding Classification, and is diagnosed based on a combination of: 1) clinical deterioration, 2) imaging findings, and 3) causal relatedness assessment. Clinical deterioration is defined as any of the following conditions: 1) NIHSS score increased more than 4 points than that

immediately before worsening; 2) NIHSS score increased more than 2 points in one category; 3) Deterioration led to intubation, hemicraniectomy, external ventricular drain placement or any other major interventions. The imaging criteria are presence of parenchymal hematoma type 2 (PH2), parenchymal hematoma type 1 (PH1), remote intracerebral haemorrhage (RIH), subarachnoid haemorrhage (SAH), intraventricular haemorrhage (IVH), or subdural haemorrhage. When clinical deterioration and PH2 co-occur, the event is automatically categorized as SICH. When clinical deterioration and PH1/RIH/SAH/IVH/SDH co-occur, the event is deemed SICH if it is judged that the haemorrhage contributed substantially to the clinical worsening. When clinical deterioration occurs only with haemorrhagic infarction type 1 or 2 (HI1 or HI2), the event is automatically classified as not SICH. ICH.

### **15.3.2 Secondary Safety Endpoints**

- Proportion of patients with any radiologic intracranial haemorrhage within 48 hours after treatment;
- Proportion of patients with pneumonia;
- Proportion of patients with gastrointestinal haemorrhage within 7 days after EVT;
- Incidence of serious adverse events.
- Incidence of any adverse events.

## **16. Assessment**

## **16.1 Assessment of efficacy**

### **16.1.1 The modified Rankin Scale (mRS)**

The mRS score is a valid and reliable clinician-reported measure of global disability that has been widely applied for evaluating recovery from stroke. It is a scale used to measure functional recovery (the degree of disability or dependence in daily activities) of people who have suffered a stroke. mRS scores range from 0 to 6, with 0 indicating no residual symptoms; 5 indicating bedbound, requiring constant care; and 6 indicating death. The mRS score will be obtained at

Day 90. Premorbid mRS status will also be obtained retrospectively and reported on the 24 Hours CRF page. In this trial, we will keep video and voice recording versions of mRS score except those who die, unable, or refuse to take a video. For mRS score at Day 90, the mRS score will be assessed by two independent certified neurologists in a blinded manner with the video combined with voice record. For those who decline to participate in a video recording, the outcomes will be determined in person by site neurologists blinded to the treatment assignment, and keep a chat record with site neurologists. Disagreements are resolved by consensus.

The mRS will only be scored by those who have been trained and certified to use this scale using the table below. (See appendix 1)

[figure not shown]

